### Interventions

#### Interventions per study arm

Eligible feet will be randomized 1:1 between group A: 22-gauge needle and group B: 15-blade group for their Achilles tendon tenotomy. Group A will undergo an Achilles tendon tenotomy with a 22-gauge needle according to our previously described protocol. The complete surgical technique can be found in Syed et al. [16] Group B will have an Achilles tendon tenotomy according to the standard protocol using a blade. A complete description and overview of the standard technique using a blade can be found in Mosca et al. [24].

Both the needle tenotomy and the blade tenotomy are performed with the patient awake and in supine position. Local anesthesia (lidocaine 1%) is injected 1 cm above the insertion of the Achilles tendon on the calcaneum, 5 min before the tenotomy is performed. The heel is disinfected with betadine, and the foot is kept maximally dorsiflexed so that the Achilles tendon is taut.

If the patient’s foot is randomized to group A, the provider will introduce a 22-gauge needle perpendicular to the coronal plane 1 cm above the insertion of the Achilles tendon on the calcaneum. The tendon fibers will be cut using the tip of the needle in a medial to lateral fashion. After about 2–3 “cuts,” all tendon fibers will be cut, and the provider will appreciate the typical “pop” when the tendon is cut completely.

Damage to the neurovascular bundle is avoided by mimicking the blade tenotomy technique with the needle, which has proven to be safe. By introducing the needle from the medial side of the ankle at the level of the Achilles tendon, the needle is introduced at about 1 cm distance of the medial neurovascular bundle. This way the chance of the needle damaging the neurovascular bundle is much lower because the needle is being introduced in a direction away from the neurovascular bundle. Secondly, the cutting movement is made from in anterior to posterior fashion only when the needle tip is clearly touching the tendon. This way, the cutting movements are away from the neurovascular bundle and any brisk or uncontrolled movement would result in the needle perforating the lateral skin or the posterior skin of the heel but not towards the neurovascular bundle.

If the patient’s foot is randomized to group B, the provider will perform the standard blade tenotomy as described by Ponseti [1]. The blade is introduced into the tendon in a perpendicular way from the medial side. The blade is held parallel to the coronal plane during insertion and rotated 90° once inserted into the tendon. The tendon is then cut with one controlled cut of the blade from cutting from the deep to the superficial part of the tendon. The provider will appreciate the typical “pop” when the tendon is cut completely.

After the tenotomy, irrespective of the technique, a sterile gauze will be put over the insertion site where the tenotomy was done. The patient then receives the standard above-knee cast with the foot put in maximal dorsiflexion. The cast is removed after 3 weeks according to standard protocol. At 3 weeks and 3 months post-tenotomy, ankle dorsiflexion and Pirani scoring are measured as per standard protocol at the Pehla Qadam clubfoot clinic.

#### Choice of comparators

The comparator chosen in this study to proof non-inferiority of the needle tenotomy technique is the gold standard 15-blade technique. We chose to compare with the gold standard to assure that participants in this trial receive appropriate care for their clubfoot and to avoid over-estimating the efficacy of the needle tenotomy. If non-inferiority of the needle tenotomy compared to the gold standard can be proven, we can assure that patients who would receive a needle tenotomy did not receive an inferior or mediocre care compared to the care that they could be receiving if they were to receive a tenotomy with a 15 blade.

We opted for a use of a 22-gauge needle, as described in our surgical technique adapted to low-resource settings [16]. A 22-gauge needle is readily available in the clubfoot clinic, of low cost, and will leave a smaller scar mark while still offering sufficient rigidity to safely cut the tendon.

#### Modification in allocated interventions

Cross-over between groups is not allowed in the trial. If a change of intervention is deemed necessary by the treating physician after group allocation, the patient will be removed from the trial and receive the appropriate care deemed necessary by their treating physician.

#### Adherence to treatment in trial participants

Adherence to casting and brace wearing after tenotomy is a paramount to the overall success of the Ponseti treatment [1]. All patients at the Pehla Qadam clubfoot clinic receive counseling about the importance of adherence to the prescribed treatment. Patients in the trial will not receive any additional interventions to increase adherence beyond what is already offered as part of the standard treatment regimen.

#### Concomitant care

All patients are allowed to receive concomitant care as deemed necessary by their treating physician. In case concomitant care requires the removal of the cast during the first 3 weeks after tenotomy, and no new cast can be applied within 24 h of removal, the patient will be removed from the trial.

### Intervention allocation

The Indus Hospital Research Center (IHRC) will prepare 244 randomization envelopes according to the SNOSE-protocol [25] at their office before the start of enrollment of patients in the clinic. Only the exact number of envelopes necessary to carry out this study will be prepared. The envelopes are sequentially numbered and contain group allocation information for the patient allocation. Group information will be inserted in the envelopes using permutated blocks of random sizes according to the SNOSE-protocol (sequentially numbered, opaque sealed envelopes) [25]. The application of the SNOSE-protocol makes it impossible to predict which group allocation will be in the upcoming envelope when allocating envelopes according to their sequential numbering and thus protects concealment of the group allocation. However, this technique also assures a 1:1 randomization of the participants at the end of the study.

All patients who meet the inclusion criteria and have an informed consent form signed by a parent will be randomized. Randomization of patients and group allocation will happen in the clinic before the tenotomy takes place. No stratification of patients takes place during the group allocation process. Each envelope will contain a piece of aluminum foil, a piece of carbon paper, and a paper containing group information.

The study team member takes the envelop with the next available sequence number when a new patient registers for the study. Before opening the envelope, a study team member will write the MR number, name, date, and study ID of the patient on the envelope. The carbon paper inside the envelope will transfer the patient details onto the paper inside the envelope, avoiding any possibility for fraud or accidental group misplacement.

In case of retraction of informed consent for the study or surgical procedure, the envelope will be returned to IHRC. When all available envelopes have been used, IHRC will provide a new set of randomization envelopes, equal to the number of returned envelopes. This procedure assures that 1:1 randomization is maintained throughout the study.

### Blinding

#### Blinding/masking

Assessment of primary and secondary outcomes will be assessed by clinical officer on duty at the Pehla Qadam clubfoot clinic and will be blinded to group allocation. The medical officer sees all children attending the clinic and will not be aware if the child is enrolled in the trial and in which group his/her foot/feet are randomized and if the child received an Achilles tendon tenotomy or not. The program coordinator will extract the necessary data for the trial from the Pehla Qadam logbooks after every clinic day as to protect the blinding at the assessor level during clinic.

Given the nature of the intervention, the physician doing the tenotomy cannot be blinded to group allocation. Parents/caregivers can be informed about group allocation if they wish to know, at the time the tenotomy is performed.

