**Methods:**

We will randomize 244 feet into group A: needle tenotomy or group B: blade tenotomy. Randomization will be done using a block randomization with random block sizes and applying a 1:1 allocation to achieve an intervention and control group of the exact same size. Children will be evaluated at 3 weeks and 3 months post-tenotomy for primary and secondary clinical outcomes. The primary clinical outcome will be the range of dorsiflexion obtained the secondary clinical outcomes will be frequency of minor and major complications and Pirani score. The non-inferiority margin was set at 4°, and thus, the null hypothesis of inferiority of the needle technique will be rejected if the mean difference between both techniques is less than 4°. The statistical analysis will use a multi-level mixed effects linear regression model for the primary outcomes and a multi-level mixed effects logistic regression model for the secondary clinical outcomes. The physician performing the evaluations post-tenotomy will be the only one blinded to group allocation.

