Percutaneous needle tenotomy has been widely described in literature as an alternative technique to the blade tenotomy with very favorable results in a population before walking age [11–15]. The original technique described by Minkowitz et al. uses a large-gauge (16–19 G) needle to percutaneously cut the Achilles tendon [12, 15]. We adapted the technique for use in a low-resource setting using a 22-gauge needle [16]. Although bleeding has been reported following this technique with similar rates as for the percutaneous blade technique, no major complications have been reported in the literature as yet [12, 15]. The needle tenotomy technique is easy to use and easy to teach to clinicians who are new to the Ponseti treatment and shown to instill less anxiety in parents and caregivers compared to a blade tenotomy [15].

Inaccessibility of Ponseti clubfoot care and non-adherence to the Ponseti protocol remain big challenges in low- and middle-income countries [17, 18]. Lack of providers, long distance to clinics, and parental fear for the tenotomy are major underlying issues generating lack of access to Ponseti care [15, 17, 18]. Introducing needle tenotomies in areas with a low density of orthopedic providers by training non-surgeons to perform the tenotomy may be a gamechanger in making Ponseti care more accessible throughout the world.

The majority of reports on the needle tenotomy technique constitute case series without an active comparator [11]. To date, only one small randomized control trial comparing percutaneous needle versus blade tenotomy has been published including 55 feet [13]. The authors did not find any significant statistical difference between the two groups (*p* > 0.05). No information detailing achieved dorsiflexion post-tenotomy, the demographics of the included participants, how the sample size was determined, nor the randomization strategy were reported. A correctly sampled non-inferiority trial comparing needle tenotomy and blade tenotomy is necessary to establish the non-inferiority of the needle tenotomy to assure that introducing this technique around the globe is safe, ethical, and effective.

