#### Emergency unblinding

Emergency unblinding is not applicable in this trial. The medical officer assessing the patient’s foot/feet at 3 weeks and 3 months post-tenotomy is the only provider blinded to group allocation in this trial. If he/she believes the child requires additional assessment, because of inadequate progression during treatment, he/she can refer the child to the treating orthopedic surgeon for further assessment. The treating orthopedic surgeon is aware of the group allocation and will do all necessary assessments and will put the child’s health before the trial. This may include unenrolling the child from the trial, if necessary. The medical officer on duty will remain blinded to the group allocation for this respective child.

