### Data collection

#### Data collection methods and participant retention

The primary and secondary outcome data collected for this trial is data that is already being collected as part of the standard follow-up of clubfoot patients at the Pehla Qadam clubfoot clinic. Therefore, no additional interventions will be done to increase the retention of participants beyond the counseling already offered to parents/caregivers of a child with clubfoot.

Assessors will not require any additional training beyond the training they receive to assess children in the clinic. The program coordinator will extract the necessary data for the trial from the Pehla Qadam logbooks after each clinic day and record it in the data tracking sheet.

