#### Analysis population and missing data

We will test for non-inferiority using the “intention-to-treat” approach. All participants will be assessed as part of the group they were randomized to. Children who were randomized to group A: needle tenotomy and received a blade tenotomy instead because of a decision made at the treating physician’s discretion are excluded from the trial. Cross-overs from the blade to the needle tenotomy group are not a possibility in our trial, given that the blade tenotomy is the gold standard and the “experimental” needle tenotomy is not performed based on parents’ request or physician’s preference. Therefore, there is no valid reason to assess the data in a “per-protocol” fashion.

As stated earlier, given the follow-up duration of 1 year, we expect a drop-out rate of about 10%, and the sample size will be adjusted for this expected loss-to-follow-up. Previous research shows that drop-out is predominantly related to a mix of socio-economic and contextual factors and much less related to the level of correction of the deformity or the satisfaction of the parents [18, 23]. Missing data is therefore considered to be missing at random (MAR) and no dummy variable creation or imputation will be done as the mixed effects regression models provide valid estimates under MAR.

Children who missed out on both follow-up consultations and for whom we were not able to schedule a follow-up consultation within 6 months of the tenotomy will be excluded from the trial.

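### Parents may be told the allocation at the tenotomy, which leaves an open route by which the only blinded person, the outcome assessor, can learn the arm

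*Protocol article*

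**What the plan says.** The protocol article (Blinding/masking) sets this rule for families: "Parents/caregivers can be informed about group allocation if they wish to know, at the time the tenotomy is performed". The same section explains that the operating physician cannot be blinded. It gives no reason for offering the allocation to parents.

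Only one person is blinded. The abstract (Methods) says: "The physician performing the evaluations post-tenotomy will be the only one blinded to group allocation". Emergency unblinding says of the medical officer who examines the feet at 3 weeks and 3 months that he or she "is the only provider blinded to group allocation in this trial".

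Blinding/masking protects the assessor in two ways. First, "The medical officer sees all children attending the clinic and will not be aware if the child is enrolled in the trial"; the officer is also not to know the group, or whether a tenotomy was done. Second, the program coordinator takes the trial data from the clinic logbooks after the clinic day, so the assessor does not handle trial records.

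The Outcomes section makes dorsiflexion at 3 months the primary outcome. Table 1 records it in 5° increments, and the non-inferiority margin is 4°.

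**The concern.** Both safeguards act on information held by staff. Neither acts on the caregiver, who may know the arm from the day of the procedure. The children are at most 36 months old, so a caregiver can be expected to be in the room at both follow-up examinations. One remark about the needle or the blade tells the assessor the technique for that child, and also that the child had a tenotomy.

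This matters more here than in many single-blind trials. Blinding of the assessor is the only masking the trial has. The outcome is a clinical reading by that same person on a coarse scale, and one step on that scale (5°) is larger than the whole margin (4°). An assessor who knows the arm and is choosing between two adjacent steps could be influenced, even without intent.

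The point concerns a rule that the protocol states, not a detail that the article leaves out.

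**Working it through.** **1. Who knows what, as written**

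| Person | Knows the arm? | Source |
|---|---|---|
| Operating physician | Yes, unavoidably | Blinding/masking |
| Treating orthopedic surgeon | Yes | Emergency unblinding |
| Parent or caregiver | Yes, on request, on the day | Blinding/masking |
| Assessor at 3 weeks and 3 months | No | Abstract; Blinding/masking; Emergency unblinding |

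The described protections cover the route from staff and records to the assessor. The route from parent to assessor is not addressed.

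**2. The plan's own sample size**

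Inputs from Sample size and power calculation: margin 4°, SD 9.02°, alpha 5%, power 95%. One-sided testing comes from the Outcomes part of the statistical methods. A true difference of 0 is assumed.

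n per arm = 2 × (1.645 + 1.645)² × 9.02² / 4² = 110.1, rounded up to 111, or 222 feet in total. This matches the stated figure. A one-sided 2.5% level would give 133 per arm (266) and does not match, so one-sided 5% is used below.

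**3. Standard error of the difference**

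SE = 9.02 × √(2/111) = 1.21°. This treats feet as independent, as the plan's calculation does.

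**4. Illustrative shifts (assumed; not taken from the documents)**

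If knowing the arm moves the reading by one 5° step in a share p of the feet in one arm, the mean difference shifts by s = 5p:

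- p = 5%: s = 0.25°
- p = 10%: s = 0.5°
- p = 20%: s = 1.0°

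**5. Effect on the two error rates**

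- Shift towards the needle, true deficit 4°: P(declare non-inferiority) = Φ(−1.645 + s/1.21).
- Shift against the needle, true difference 0°: power = Φ((4 − s)/1.21 − 1.645).

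| Shift s | False non-inferiority (shift towards needle) | Power (shift against needle) |
|---|---|---|
| 0° | 5% | 95% |
| 0.25° | 7.5% | 92.7% |
| 0.5° | 10.9% | 89.4% |
| 1.0° | 20.6% | 79.8% |

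The table shows how sensitive the conclusion is to small reading shifts. It does not estimate how often disclosure will happen or which way it would act.

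**The case against.** **This is a declared design.** The trial calls itself single-blinded throughout, so parents knowing the arm contradicts nothing. Assessor blinding has real protections, and a remark by one parent unblinds one child's reading, not the trial. All of this stands, and it limits the point to a weakness. It does not close the route from parent to assessor.

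**The information sheet is not shown.** It is Additional file 1 and may already ask parents not to discuss the technique. That cannot be checked, so the absence of such a request from the article is not held against the plan. What can be held against it is the rule that allows disclosure on the day.

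**The shifts are invented.** They are, and they could go either way. That is why both directions are given.

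**A stronger reading.** A reader might infer that informed parents will also attend or brace differently by arm, and that this favours the needle. The raw material for that inference is in the article. Background says the needle was "shown to instill less anxiety in parents and caregivers compared to a blade tenotomy", and the section on adherence says: "Adherence to casting and brace wearing after tenotomy is a paramount to the overall success of the Ponseti treatment". Under data collection, "no additional interventions will be done to increase the retention of participants beyond the counseling already offered". The inference is still not supported, for four reasons:

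- No section links knowing the instrument to later attendance, brace use or withdrawal. Background names parental fear as a barrier to reaching care, whereas parents in the trial have already consented to a tenotomy on the same day.
- Analysis population and missing data addresses the mechanism. It says "drop-out is predominantly related to a mix of socio-economic and contextual factors and much less related to the level of correction", and the sentence goes on to put parents' satisfaction alongside correction as a lesser influence.
- That section assumes data are missing at random, not that loss is unrelated to treatment. With arm in the model, different rates of loss by arm are not in themselves a bias.
- Losing more blade feet would widen the confidence interval and make non-inferiority harder to show. It would help the needle only if the lost feet would have done better than those retained. Anxious parents might also brace more carefully, not less.

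**Conclusion.** The point holds as a gap in the protection of assessor blinding. The protocol lets parents learn the arm at the tenotomy, makes the assessor the only blinded person, and describes safeguards that do not reach the parent. The reading at risk is the primary outcome.

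The size and direction of any bias are unknown. Under the assumed shifts of 0.25° to 1.0°, false non-inferiority at a true 4° deficit would be about 7.5% to 21% instead of 5%, or power would be about 93% to 80% instead of 95%. These figures rest on the plan's SD of 9.02°, 111 evaluable feet per arm, independent feet and a one-sided 5% test. The sample size is not affected.

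No claim is made that attendance or brace use will differ by arm, or that the rule favours the needle.

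**What to change.** Change the rule in Blinding/masking, and bring the information sheet into line with it:

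1. Do not routinely offer the allocation to parents until after the 3-month assessment, where this is feasible and unless the child's care needs it sooner.
2. Ask parents not to name the instrument to the person examining the foot at 3 weeks and 3 months.
3. Record any disclosure to the assessor and report the number by arm.

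An analysis without the disclosed feet may be shown, but as description only. Disclosure happens after randomisation and may differ by arm, so leaving those feet out can itself introduce bias.

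The cost is a few sentences and a simple log. Some parents will wait about three months to be told, and some will have seen the instrument anyway. Because the change affects what families are told, it may need a formal amendment and IRB approval under Protocol amendments. Trial status puts the start of enrolment in May 2021 and its expected end in September 2023, so a change late in enrolment reaches fewer families. For feet not yet assessed, asking parents not to name the instrument and logging disclosures remain possible.

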#### Emergency unblinding

Emergency unblinding is not applicable in this trial. The medical officer assessing the patient’s foot/feet at 3 weeks and 3 months post-tenotomy is the only provider blinded to group allocation in this trial. If he/she believes the child requires additional assessment, because of inadequate progression during treatment, he/she can refer the child to the treating orthopedic surgeon for further assessment. The treating orthopedic surgeon is aware of the group allocation and will do all necessary assessments and will put the child’s health before the trial. This may include unenrolling the child from the trial, if necessary. The medical officer on duty will remain blinded to the group allocation for this respective child.

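### A surgeon who knows the allocation may unenrol a child for inadequate progress at 3 weeks, before the 3-month primary endpoint, and the protocol does not say the child is still measured or analysed

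*Protocol article*

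**What the plan says.** **Emergency unblinding.** The blinded medical officer assesses the foot at 3 weeks and 3 months. If more assessment seems needed, "because of inadequate progression during treatment, he/she can refer the child to the treating orthopedic surgeon for further assessment". Then: "The treating orthopedic surgeon is aware of the group allocation and will do all necessary assessments". The section adds: "This may include unenrolling the child from the trial, if necessary". It gives no criterion for unenrolment.

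**Concomitant care.** If other care requires the cast to come off in the first 3 weeks and "no new cast can be applied within 24 h of removal, the patient will be removed from the trial".

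**Analysis population and missing data.** The non-inferiority test is declared to be by intention to treat: "All participants will be assessed as part of the group they were randomized to". This section names two exclusions: needle-to-blade conversions, and children who miss both follow-up visits and cannot be seen within 6 months. It does not mention unenrolment by the surgeon or removal after loss of the cast. It assumes data are missing at random because drop-out is mainly socio-economic and much less related to the degree of correction. No imputation is planned.

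**Trial design; Outcomes.** The primary endpoint is dorsiflexion at 3 months. Table 1 gives the 3-week and 3-month values separate rows. The only random effect described under Data analysis is for the child, to handle paired feet.

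Conversion at the time of tenotomy ("If a change of intervention is deemed necessary by the treating physician after group allocation, the patient will be removed from the trial") is a different route out of the trial and is not the subject of this point.

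**The concern.** Inadequate progression after a tenotomy is a poor result on the quantity being compared. A child referred for it at 3 weeks can leave before the 3-month value is taken, on the decision of someone who knows the arm. If one technique leaves more poor results, more of its feet meet the trigger. The feet that remain then look more alike than the randomised groups really are, and in a non-inferiority trial that favours the claim. A foot that leaves because of poor progress is also not the kind of loss on which the missing-at-random argument rests.

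**Working it through.** **1. Can removal depend on the outcome and come before the endpoint?**

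| Route | Trigger | Who decides | Before the 3-month value? |
|---|---|---|---|
| Referral at 3 weeks, then unenrolment | Inadequate progression | Surgeon who knows the arm, at discretion | Yes |
| Referral at 3 months, then unenrolment | Inadequate progression | Same | No; the outcome is measured at that visit |
| Cast off, none replaced within 24 h | Concomitant care, first 3 weeks | Fixed 24 h limit | Yes, but the trigger is not itself a poor outcome |

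Only the first row is clearly outcome-related and early. The third could follow an infection or neurovascular problem, which the Outcomes section classes as major complications, but Concomitant care does not say so.

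**2. The plan's own figure.** Sample size section: one-sided alpha 5%, power 95%, margin 4°, SD 9.02°.

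n per arm = 2 × (1.645 + 1.645)² × 9.02² / 4² = 110.1, rounded up to 111, or 222 feet. This matches. The standard error of the difference is 9.02 × √(2/111) = 1.21°.

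**3. Illustration with a common cut at 3 weeks.** Assumptions, not in the protocol:
- The true needle deficit is exactly 4°, so the false-claim rate should be 5%.
- The blade mean is 21.42° (the protocol's literature mean) and the needle mean 17.42°, at both visits.
- Values are normal and feet independent; the 5° recording steps are ignored.
- The correlation ρ between visits is 0.5 to 0.9.
- Every foot below the cut c at 3 weeks leaves, in both arms, and the remaining 3-month values are compared.

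For each arm with mean μ, let a = (c − μ)/9.02, proportion removed q = Φ(a), and λ = φ(a)/(1 − q). Then:
- mean of remaining feet = μ + ρ × 9.02 × λ
- variance of remaining feet = 9.02² × [1 + ρ²(aλ − λ²)]
- feet remaining = 111 × (1 − q)
- P(claim) = Φ((4 − d)/s − 1.645), where d is the apparent deficit and s its standard error.

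Worked case, c = 5°, ρ = 0.7:
- Blade: a = −1.820, q = 3.4%, λ = 0.0788, mean 21.42 + 0.7 × 9.02 × 0.0788 = 21.92°, SD 8.68, 107.2 feet.
- Needle: a = −1.377, q = 8.4%, λ = 0.1688, mean 17.42 + 0.7 × 9.02 × 0.1688 = 18.49°, SD 8.42, 101.6 feet.
- d = 3.43°, s = √(8.68²/107.2 + 8.42²/101.6) = 1.18°.
- P(claim) = Φ(0.57/1.18 − 1.645) = about 12%.

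| 3-week cut | Removed, blade / needle | Apparent deficit, ρ = 0.5 to 0.9 | False claim |
|---|---|---|---|
| none | 0 / 0 | 4.00° | 5% |
| 0° | 0.9% / 2.7% | 3.82° to 3.68° | 7% to 9% |
| 5° | 3.4% / 8.4% | 3.59° to 3.27° | 9% to 16% |
| 10° | 10.3% / 20.5% | 3.29° to 2.71° | 14% to 31% |

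**4. Dependence on which arm loses feet.** Suppose instead that the lowest fraction q is removed on the 3-month scale itself. The arm mean then rises by 9.02 × φ(z_q)/(1 − q), where z_q is the normal quantile at q.
- Needle arm only, 2% (0.02 × 111 = about 2 feet): shift 0.45°, apparent deficit 3.55°, false claim about 10%.
- Needle arm only, 5%: shift 0.98°, apparent deficit 3.02°, false claim about 21%.
- Equal proportions in both arms: the shifts cancel, the deficit stays 4.00° and the error stays 5%.

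**5. Would a missing-at-random model repair it?** In step 3 removal depends only on the 3-week value, which was measured. An estimate that uses those values recovers a deficit of 3.98° to 4.01°. That repair needs the 3-week values to be kept and modelled jointly with the 3-month values. Table 1 states no such model.

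**The case against.** The strongest reply is that the protocol only says unenrolment may happen, if necessary, as part of putting the child's health first. That stands: it is discretionary and may be rare. The nearest figure in the Background is about 4% of blade patients not reaching 15° at 1 year and needing re-tenotomy, so the 10° cut is toward the high end. Several stronger readings are tempting, but the text does not support them.

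- **Poor results are deleted.** A reader might infer this. Data management provides for destroying data only when consent is retracted. Nothing says that values already recorded for an unenrolled child are discarded; equally, nothing says they are used.
- **Both visits are affected.** A referral at 3 months comes at the visit where the primary outcome is measured, so only the 3-week referral can pre-empt it.
- **The cast rule removes bad outcomes at the surgeon's choice.** Its trigger is concomitant care with a fixed time limit. Harms also have a separate recording route under Harms and adverse events.
- **Missing-at-random methods cannot help.** Too absolute: step 5 shows that a joint model would absorb removal driven only by the 3-week value. It would not absorb a decision that also rests on the surgeon's further assessments and knowledge of the arm.
- **The false-claim rate could be about 92%.** That arises only if 25% of needle feet fail at about 5° and every one is removed, with none from the blade arm. Nothing in the protocol supports those inputs.

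What is left unanswered is that no section keeps an unenrolled child in follow-up or in the analysis.

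**Conclusion.** The point holds in this form. The protocol permits outcome-related removal after treatment, by a clinician who knows the allocation, between the 3-week visit and the 3-month endpoint. That conflicts with its intention-to-treat statement and is not covered by its reason for assuming missing at random. The cast-removal rule is a lesser conflict of the same kind.

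The direction is toward non-inferiority if more needle than blade feet leave for poor results. A single rule applied to both arms has that effect when the needle is truly worse, because more needle feet fall below any cut. The size is unknown, since no removal rate is given. Under the stated assumptions the 5% error becomes about 7–9%, 9–16% or 14–31% for cuts at 0°, 5° or 10°. These figures show sensitivity; they do not predict what will happen. The required sample size of 222 feet is unaffected.

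**What to change.** Reconcile Emergency unblinding and Concomitant care with Analysis population and missing data. State in each that:

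1. Clinical care remains the physician's decision, and unenrolment or cast removal ends trial procedures only.
2. Every treated foot stays in its randomised arm, its routine 3-week and 3-month data are still extracted, and it enters the primary and complication analyses unless consent is withdrawn.
3. The reason and date of each such event are recorded and reported by arm.
4. Feet with a repeat tenotomy before 3 months are flagged. Harms and adverse events foresees re-performing the tenotomy after 3 weeks; the 3-month value then reflects the second procedure, which can itself favour non-inferiority. Add a sensitivity analysis, for example using the last value before the repeat procedure.

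The cost is protocol and analysis-plan wording. The visits and measurements are already routine in the clinic and are taken from its logbooks. The downsides are that a few deviating feet add some variance to the primary analysis and one sensitivity analysis has to be specified.
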